### Other measurements and assessments

#### Baseline characteristics

Baseline characteristics (age, sex, diagnosis, height, weight) of participants will be recorded at the beginning. These are retrieved via the clinic’s internal software program. In addition, the socio-economic status is queried using the Family Affluence Scale [106].

#### Chemotherapy intensity and therapy protocol

Chemotherapy intensity, classified into four levels based on the duration of severe neutropenia will be assigned to each participant using their clinical records [107, 108]. Furthermore, the patient’s therapy protocol will be documented.

#### Feasibility

For quality assurance purposes, feasibility and implementation outcomes will be assessed using a self-developed questionnaire. Further, a subsample of participants will be qualitatively interviewed using semi-structured interviews, which will be transcribed and analyzed with qualitative content analysis.

### Statistical analysis

#### Sample size calculation

Two sample size calculations were performed for the primary outcomes: one encompassing both inhibition and cognitive flexibility and another for working memory. The calculation for the former is presented below, as it yielded the larger sample size needed, which was therefore selected for the study.

The sample size calculation was done using G*Power 3: Repeated measures ANOVA with four measurement points and two groups (within-between interaction), a statistical power of 80%, a small effect size (Cohen’s *f* = 0.105) [54], an α = 0.05 and a retest correlation of 0.8. This results in a minimum sample size of *N* = 52 in total, i.e. 26 subjects per group. To compensate for losses and drop-outs, we set the minimal sample size to *N* = 70.

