### Participants

In total, a minimum of 70 participants (for details, see sample size calculations), will be included, with 35 assigned to the intervention (IG) and 35 to the control group (CG).

Children and adolescents aged 6–17 years with a diagnosis of any type of cancer requiring chemo- and/or radiotherapy, expected to last a minimum of at least six weeks at the time of recruitment, and/or CNS surgery, will be included.

Participants will be excluded if they have cognitive and physical disabilities (e.g. down syndrome, cerebral palsy), that prevent participation in the intervention. Additionally, the inability to follow the procedures of the study, e.g. due to language problems, is an exclusion criterion.

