#### Executive Functions (EFs)

The following table provides a summary of three cognitive function tests, detailing their primary purpose, task procedure, duration, target age group, and key outcome measures. These tests assess the three core EFs, including inhibition, cognitive flexibility and working memory. They have been validated across different age ranges. (Table 2). 

**Table 2 Tab2:** Summary of the primary outcome measurements (EFs)

Test Name	Cognitive Function Assessed	Task Description	Duration (minutes)	Age Range (years)	Outcome Measures	Reliability	Ref.
Hearts and Flowers Task	Inhibition and cognitive flexibility	Participants sit facing a screen and respond by pressing a button on the corresponding side when a heart stimulus appears and on the opposite side when a flower stimulus is displayed. Three blocks: congruent (hearts), incongruent (flowers), and mixed (both).	5	4–45	Reaction time, accuracy, composite score	Cronbach’s alpha = 0.83 Test-retest reliability: 0.62 for accuracy score 0.72 for reaction time	[10, 57–61]
Fish Flanker Task	Inhibition	Participants sit in front of a screen and respond to the orientation of a central fish while ignoring surrounding fish, which may show in congruent or incongruent directions.	8	6–18	Reaction time, accuracy, composite score	ICC = 0.92	[62, 63]
Digital Corsi Block Task	Visuospatial working memory	Participants replicate sequences of illuminated blocks on a digital screen, with increasing sequence length in case of correct responses.	varies	>7	Block span, total correct sequences, summary score	ICC = 0.93 for children, ICC = 0.76 for adolescents	[64–69]

*ICC* Intraclass correlation coefficient

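### The sample size assumes a retest correlation of 0.8, which Table 2 does not support for the two Hearts and Flowers scores it reports, so 80% power with 52 completers is unsupported for them

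*Protocol article*

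**What the plan says.** Under Sample size calculation, the protocol article reports two calculations for the primary outcomes: one for inhibition and cognitive flexibility together, one for working memory. It presents the first because it needed the larger sample. The design is "Repeated measures ANOVA with four measurement points and two groups (within-between interaction"), with 80% power, Cohen's f = 0.105, and "an α = 0.05 and a retest correlation of 0.8". The reference in that sentence follows the effect size; nothing is cited for the correlation. The result is given as "This results in a minimum sample size of *N* = 52 in total, i.e. 26 subjects per group", and then: "To compensate for losses and drop-outs, we set the minimal sample size to *N* = 70". The Participants section splits the 70 equally, 35 per group.

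Under Executive Functions (EFs), Table 2 lists three tests. Hearts and Flowers covers inhibition and cognitive flexibility and yields reaction time, accuracy and a composite score. Its entry reads "Test-retest reliability: 0.62 for accuracy score 0.72 for reaction time", next to a Cronbach's alpha of 0.83. Fish Flanker covers inhibition only, with an ICC of 0.92. The Corsi task covers working memory and belongs to the other calculation.

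**The concern.** The presented calculation claims to cover cognitive flexibility, and only Hearts and Flowers measures it. Both retest values that the protocol prints for that test lie below the correlation on which the sample size rests. In a repeated-measures interaction test the noncentrality is proportional to 1/(1 − ρ), so a modest drop in ρ costs a good deal of power. Executive function is the primary objective. If the 80% figure is carried into the report without qualification, a null result on Hearts and Flowers could be taken as evidence from an adequately powered comparison when, for accuracy or reaction time, it may not be. The allowance for drop-out (52 to 70) may also be spent on the correlation before anyone is lost.

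**Working it through.** **Inputs from the protocol article.** f = 0.105, α = 0.05, 80% power, m = 4 visits, k = 2 groups and ρ = 0.8 (Sample size calculation). Alternative ρ values: 0.72, 0.62 and 0.92 (Table 2).

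**Assumption.** Sphericity (ε = 1). The article does not state it, but it reproduces the stated N.

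**Formula.** λ = f² · N · m / (1 − ρ), with df1 = (k − 1)(m − 1) = 3 and df2 = (N − k)(m − 1) = 3(N − 2). Power is the probability that a noncentral F with these parameters exceeds the 5% critical value.

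**Step 1: the plan's own figure.** f² = 0.011025. At N = 52, f² · N · m = 0.011025 × 52 × 4 = 2.2932, so λ = 2.2932 / 0.20 = 11.47 and power is 81.1%. At N = 50 power is 79.3%. The smallest even N reaching 80% is therefore 52, as stated.

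**Step 2: the same test with the Table 2 values.** At N = 52, λ = 2.2932 / 0.28 = 8.19 for 0.72 and 2.2932 / 0.38 = 6.03 for 0.62. At N = 70, f² · N · m = 3.087, so λ = 11.03 and 8.12.

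| ρ | Source | Power, 52 completers | Power, 70 completers | N for 80% | Detectable f at 52 (80% power) |
|---|---|---|---|---|---|
| 0.80 | assumed | 81.1% | 92.0% | 52 | 0.104 |
| 0.72 | Hearts and Flowers, reaction time | 65.3% | 79.6% | 72 | 0.123 |
| 0.62 | Hearts and Flowers, accuracy | 50.9% | 65.2% | 96 | 0.143 |
| 0.92 | Fish Flanker (ICC) | 99.7% | over 99.9% | 22 | 0.066 |

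λ falls by 1 − 0.20/0.28 = 29% at 0.72 and by 1 − 0.20/0.38 = 47% at 0.62.

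**Step 3: how much tolerance there is.** For 80% power, ρ must be at least 0.795 with 52 completers, or 0.722 with 70. The planned loss is 1 − 52/70 = 25.7%. At 0.72 the whole reserve of 18 is needed to reach about 80%.

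**Step 4: what f = 0.105 means at T2.** Let d_t be the group difference at visit t in SD units. With two equal groups, f is half the standard deviation of d_t over the four visits (divisor 4), so that standard deviation is 0.21. The T2 difference then depends on the time pattern:
- Growing linearly in weeks (0, 6, 12 and, by assumption, 26): 0.26 SD.
- Growing equally from visit to visit: 0.38 SD.
- Half the effect at T1, full at T2, then fully kept or fully lost at T3: 0.51 SD.
- Half at T1, full at T2, half at T3: 0.59 SD.

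So f = 0.105 does not correspond to a single T2 difference.

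**The case against.** The case on the other side has several parts.

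- **Fish Flanker.** The calculation covers two tests, and 0.8 lies inside their joint range of 0.62 to 0.92. Averaging the Hearts and Flowers values (0.67) with 0.92 gives 0.795, almost exactly what 52 completers require. This stands as a limit: the shortfall does not extend to Fish Flanker. It does not rescue cognitive flexibility, because Fish Flanker does not measure it, an average does not protect the weaker test, and the article does not say that it averaged.
- **The composite score.** The analysed score may be the composite, for which no retest value is given. This stands: the document neither confirms nor refutes 0.8 for it. The alpha of 0.83 does not help, since internal consistency is not correlation between visits.
- **Age and diagnostic range.** The 6 to 17 year span and mixed diagnoses could raise the correlation between visits above a reliability-study value. This is possible. A larger between-child SD would also shrink f for the same raw effect, but whether that matters here depends on the sample behind the 0.105, which is not shown. The point stays open.
- **Analysis method.** Linear mixed models replace the ANOVA if they converge, and imputation or maximum likelihood lets partial data contribute. So 52 completers is not the only scenario, and power under the mixed model was not computed. But the 80% claim is made for the repeated-measures ANOVA, and departure from sphericity would lower its power further.

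A reader might infer that the trial as a whole does not deliver 80% power, or that the sample size was miscalculated. The documents support neither: N = 52 follows from the stated inputs, and one of the two tests covered is well powered.

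**Conclusion.** The point holds in limited form. The correlation of 0.8 has no stated source and exceeds both retest values in Table 2 for the only cognitive-flexibility test. For those two scores, 80% power with 52 completers is not supported: it is 51% (accuracy) to 65% (reaction time), rising to 65% and about 80% if all 70 complete. These figures rest on f = 0.105, sphericity, the repeated-measures ANOVA, and Table 2 retest values carrying over to this trial's visits. That last assumption cannot be tested from the document. Nothing is established against Fish Flanker or the Hearts and Flowers composite. Severity: should fix. The fault is an unsupported planning input, and correcting it leaves the design, outcomes and analysis as they are.

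**What to change.** Keep N = 70 and do one of two things under Sample size calculation:

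1. Name the Hearts and Flowers score to be analysed and give a source or reasoning that supports 0.8 for that score.
2. Otherwise, confine the 80% statement to scores with a correlation of about 0.8 or more. For Hearts and Flowers over 0.62 to 0.72, report power of 51% to 65% with 52 completers and 65% to 80% with 70, with the detectable f at 52 completers (about 0.143 down to 0.123).

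If the effect is also expressed as a T2 difference, give it as a range tied to the assumed time pattern (about 0.26 to 0.59 SD), not as one value.

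The cost is a short rewrite and a less favourable power figure for one test. No patients, visits or procedures are added.

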#### Statistical analysis plan

Study sample characteristics will be shown separately as mean values (x̄) with its standard deviation (±) for each group regarding continuous variables. For categorical variables percentages and absolute numbers will be used. Normal distribution will be analyzed by the Shapiro-Wilk test and graphical verification of the Gaussian distribution. For all analyses, the significance level will be set at *p* < 0.05 and effect sizes will be provided.

*Preliminary analyses* will be performed to ensure that characteristics of the study participants (e.g., age, sex, diagnosis, weight, height) are comparable between the IG and CG using independent *t-*tests (continuous variables) or chi-squared tests (categorical variables). For feasibility analysis, descriptive statistics will be used.

The *main analyses* for the primary and secondary outcomes are repeated measures ANOVAs (for normal distributed data) and the Friedman test (for non-normally distributed data), where the “between-group” factor describes the IG vs. CG and the “within-group” factor is “timepoint” (T0, T1, T2, T3). If linear mixed models converge (despite small sample size), they will be used instead of repeated measures ANOVAs. These models will be specified to adjust for potential baseline imbalances [109]. They include the main effect of time and the group-time interaction. As the period between the data collection waves most probably will not be equal for all participants, as a time variable, the individual time interval in days will be used to increase the precision with which a child’s growth trajectory is measured. For each dependent variable, the optimal model will be determined using likelihood-ratio tests for nested models and Akaike information criterion for non-nested models. For these comparisons a random intercept model will be compared to a fixed effects model and a model including random intercepts and fixed effects. The model with the best fit will subsequently be chosen.

For *supplementary analyses*, we will perform the same analyses for different age groups (6–11.99 and 12–17.99 years), cancer types (e.g. leukemia, brain tumors) and chemotherapy severity levels with sufficient sample size (*n* > 20). In addition, baseline performance will be correlated with gain scores using Pearson correlations (for normally distributed data) or Spearman correlations (for non-normally distributed data) for outcomes that show significant group × time interactions. To explore associated changes in certain variables, changes in motor abilities will be correlated with changes in core EFs and psychosocial functioning.

Additionally, for the intention-to-treat (ITT) analyses, we will perform two per protocol analyses. In the first per protocol analyses, only participants will be included, who did at least 80% of the PA sessions, in the second per protocol analyses participants will be included, if they completed 60% of training sessions. For all statistical analyses, the statistical program R and SPSS will be used.

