## Background

A cancer diagnosis and its treatment in children and adolescents frequently leads to physical impairments such as decline in fitness, muscle loss, and frailty [1, 2]. Over the past decades, the 10-year overall survival rate in high-income countries has significantly improved to 80% [3]. However, this improvement has shifted attention toward the potential long-term impairments associated with the disease, its treatment and the manifested reduced physical activity (PA) [4–6]. 70% of all childhood cancer survivors (CCSs) develop a chronic health condition within 30 years of cancer diagnosis [7]. The most common late effects of CCSs include cardiovascular diseases, hearing loss, renal function impairment, endocrine dysfunctions, hypothyroidism, infertility, as well as neurological and cognitive impairments [8].

Cognitive late effects, including impairments in attention, memory, and processing speed affect around 35–60% of CCSs [9]. Risk factors for cognitive impairments in pediatric cancer patients include high cranial radiation doses, large irradiated brain volume, younger age at diagnosis, and central nervous system (CNS) surgery [9]. These impairments affect particularly higher-order cognitive domains, such as executive functions (EFs) [9], which are required for performing and monitoring goal-oriented, adaptive, and flexible behavior [10]. EFs are essential in unfamiliar, complex, and demanding environments and conditions [10]. One EF model suggests three core processes of EFs (a) inhibition, (b) working memory, and (c) cognitive flexibility, that are important for inhibiting predominant responses and controlling selective attention, for processing and retaining information; and shifting between mental sets and tasks [11]. Additionally, EFs predict a wide range of developmental outcomes (self-control, frustration tolerance, physical health) and academic achievement in children [12, 13].

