## Methods

The study is an investigator-initiated, two-phase, non-randomized multicentre controlled trial. During the first phase, the intervention will commence at the Inselspital Bern, while the University Children’s Hospitals Basel and Zurich, as well as the Children’s Hospital Aarau will serve as control sites. In the second phase, after 1.5 years, the intervention will be implemented in Basel, Zurich and Aarau, with Bern serving as the control. Due to ethical considerations, randomization of participants within a single center was not feasible; therefore, the control group consists of participants from other centers.

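### In a comparison allocated by centre and period, baseline significance tests cannot establish comparability, and the stated main model leaves out the collected prognostic factors that the protocol itself names

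*Protocol article*

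**What the plan says.** **Design.** Under Methods: "The study is an investigator-initiated, two-phase, non-randomized multicentre controlled trial". Bern starts as the intervention site, with Basel, Zurich and Aarau as controls, and the roles swap after 1.5 years. The article explains that "randomization of participants within a single center was not feasible; therefore, the control group consists of participants from other centers". The planned size is 35 per group (Participants).

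**Comparability check.** Under Statistical analysis plan, preliminary t-tests and chi-squared tests "will be performed to ensure that characteristics of the study participants (e.g., age, sex, diagnosis, weight, height) are comparable between the IG and CG".

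**Main model.** Repeated measures ANOVA or the Friedman test is planned. Linear mixed models replace the ANOVA if they converge. On the mixed models the article says: "These models will be specified to adjust for potential baseline imbalances". The next sentence gives their terms as the time main effect and the group-by-time interaction. No covariate is named there or for the ANOVA, and time is to be measured in individual days.

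**What is known and collected.** The Background states: "Risk factors for cognitive impairments in pediatric cancer patients include high cranial radiation doses, large irradiated brain volume, younger age at diagnosis", and adds CNS surgery. Age, sex, diagnosis, height, weight and family affluence are recorded (Baseline characteristics), as are a four-level chemotherapy intensity and the therapy protocol (Chemotherapy intensity and therapy protocol). Age group, cancer type and chemotherapy severity return only as supplementary repeats of the analysis in strata with n > 20.

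**The concern.** With no randomisation, nothing in the design makes the two groups alike in expectation, so the analysis has to deal with confounding. Two stated elements do not do so.

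First, a significance test cannot ensure balance. In small groups a non-significant result is the likely outcome even when the imbalance is large enough to matter.

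Second, the stated model uses only the outcome's own baseline. It does this by leaving out a group main effect, which gives both groups the same expected baseline. Factors that change the course of executive function over the twelve weeks, such as age or CNS-directed treatment, are not held constant. If one group has more children with CNS tumours or more young children, their different course is read as an intervention effect. Most of the information needed to reduce this is already being recorded.

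**Working it through.** **Inputs.** 35 per group (Participants). For the planning values, the Sample size calculation section gives f = 0.105, 80% power, four measurements and "an α = 0.05 and a retest correlation of 0.8". Imbalances, confounder strengths and the exact T3 day are not in the article and are treated as assumptions below.

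**1. The plan's own figure.** Noncentral F with λ = f²·N·m/(1−ρ), df 3 and 3(N−2), sphericity assumed. For N = 52, λ = 0.105² × 52 × 4 / 0.2 = 11.47 and power is 0.811; for N = 50 it is 0.793. The stated N = 52 reproduces. For scale, f = 0.105 corresponds to a group difference in change of about 0.48 SD (step pattern: 2 × 0.105 / 0.433) to 0.56 SD (linear pattern: 2 × 0.105 / 0.373).

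**2. What the baseline tests can detect (two-sided 0.05).**
- Continuous variable, noncentral t with noncentrality d·√(n/2). For d = 0.4: 0.4 × √17.5 = 1.673, 68 df, power 0.378, so the imbalance is missed 62% of the time. For d = 0.5, power is 0.541 (missed 46%); for d = 0.3 it is 0.236 (missed 76%).
- Proportions 20% versus 35%. The pooled SE is √(2 × 0.275 × 0.725 / 35) = 0.1067 and the unpooled SE is √((0.20 × 0.80 + 0.35 × 0.65) / 35) = 0.1052. Power = Φ((0.15 − 1.96 × 0.1067) / 0.1052) = 0.287, so the imbalance is missed 71% of the time.

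**3. What an unadjusted factor does to the effect.**
- *CNS tumours.* Assume 20% versus 35%, and that CNS patients change 0.5 SD less by T2. Bias = 0.15 × 0.5 = 0.075 SD. The SE of the group difference in change is √(2 × (1−0.8)) × √(2/35) = 0.151 SD, so the bias is 0.50 SE. The 5% test then rejects about 8% of the time with no intervention effect.
- *A continuous factor acting on the slope.* Bias per 12 weeks is about the group gap times the effect per SD: 0.3 × 0.1 = 0.03 SD, 0.5 × 0.2 = 0.10 SD, 0.5 × 0.4 = 0.20 SD. Simulation with 35 per group gave 0.03, 0.10 and 0.21 SD, practically the same with or without a group main effect. The group term therefore does not deal with this problem.

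**4. The omitted group main effect.** Generalised least squares with compound symmetry, ρ = 0.8, linear time and no intervention effect. The expected interaction slope is (ΣX′V⁻¹X)⁻¹ΣX′V⁻¹μ, and the rejection rate is Φ(z−1.96) + Φ(−z−1.96). T3 is taken at week 26 or, if the six months run from T2, at week 38.

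| Baseline gap of 0.5 SD | Group term omitted | Group term kept |
|---|---|---|
| Constant over time, T3 week 26 | 9.3% | 5.0% |
| Constant over time, T3 week 38 | 8.1% | 5.0% |
| Regresses to ρ × 0.5 SD after baseline, T3 week 26 | 5.0% | 8.3% |

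With time as categories, the T2 bias in the constant case is 0.5 × (1−0.8) = +0.10 SD when the term is omitted. In the regressing case it is −0.10 SD when the term is kept. A constant gap of 0.25 SD gives about 6% when the term is omitted.

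**The case against.** **The article may intend covariates.** It announces adjustment for baseline imbalances, its list of terms is not said to be exhaustive, it cites a source for the specification, and a fuller analysis plan may exist. That is a fair reading of the intention. But the terms are spelled out in the next sentence and no prognostic factor is among them. The point rests on those stated terms, not on missing detail.

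**The swap already helps.** Every centre contributes to both groups in turn, which offsets part of any stable difference in case mix between centres. It cannot guarantee similar patients in a sample of 70, and neither centre nor phase is a stated model term.

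**The strata cover it.** Repeating the analysis by age group, cancer type and chemotherapy severity is a useful supplement. It leaves the main estimate unadjusted.

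**The tests are only preliminary.** This stands. A reader might infer that the main analysis depends on their result; the article conditions nothing on them. The fault is the purpose claimed for them, and dropping them changes no estimate.

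**The group main effect.** A reader might infer that omitting it is a plain error, with type I error up to 16%. The documents do not support that. The 16% needs a correlation of 0.62, the Hearts and Flowers accuracy reliability, whereas the plan uses 0.8; and it needs a gap that stays constant. Baseline falls soon after diagnosis, so a partly transient gap is plausible, and then the model that keeps the term is the biased one.

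**Conclusion.** The point holds and should be corrected before the data are analysed. Tests at 35 versus 35 cannot establish comparability, and the primary comparison as stated omits prognostic factors that the protocol names and largely records. The power figures follow from the group sizes and the imbalances chosen for illustration. The bias figures (0.075 SD for the CNS example, 0.03 to 0.20 SD per 12 weeks for a factor acting on the slope) rest on assumed imbalances and strengths, since the article gives none. They are small to moderate beside the 0.48 to 0.56 SD for which the trial is sized, but could change a borderline result.

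The constrained baseline is a secondary matter. It assumes equal expected baselines, which allocation by centre does not guarantee, and costs about 8–9% type I error at the planning correlation if a 0.5 SD gap is constant. Which model is less biased depends on whether the gap persists, so this is a trade-off.

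**What to change.** 1. Replace the baseline t-tests and chi-squared tests with standardised differences between groups, and drop the claim that they ensure comparability.
2. Adjust the primary model, whatever imbalance is observed, for a short prespecified list: age; CNS tumour or cranial radiotherapy (yes/no, derived from diagnosis and therapy protocol); and chemotherapy intensity as a single score. Give each an interaction with the continuous time variable already planned. Since intensity is classified by duration of severe neutropenia, state whether the level is set from the therapy protocol at enrolment or from what is observed later.
3. Keep the constrained-baseline model as primary if preferred, and report the model with a group main effect as a sensitivity analysis.

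**Cost.** Mainly wording; the yes/no CNS variable must be derived from records already planned. Three main effects plus three time interactions make about six parameters in 52–70 children. Using four intensity levels as categories would make it ten (five main effects, five interactions). With categorical visits the count would be 12 (3 + 3 × 3) to 20 (5 + 5 × 3), which is hard to support in a model whose convergence the article already doubts. If convergence fails, keep age and CNS status only. Adjustment reduces confounding by the listed factors only; unmeasured differences between centres and periods remain.

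### Outcomes judged non-normal are sent to the Friedman test, which has no group factor, so as written they would get no test of IG versus CG

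*Protocol article*

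**What the plan says.** All references are to the protocol article.

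- *Statistical analysis plan* sets the main analyses, for primary and secondary outcomes alike, as "repeated measures ANOVAs (for normal distributed data) and the Friedman test (for non-normally distributed data". One clause then describes the factors for both: the between-group "factor describes the IG vs. CG and the" within-group factor is time point, T0 to T3.
- The branch is chosen as follows: "Normal distribution will be analyzed by the Shapiro-Wilk test and graphical verification of the Gaussian distribution". The text does not say whether raw scores or model residuals are examined.
- "If linear mixed models converge (despite small sample size), they will be used instead of repeated measures ANOVAs". Of these models it says: "They include the main effect of time and the group-time interaction". They are also meant to adjust for baseline imbalance and to use each child's elapsed days as the time variable.
- *Objectives and hypotheses* makes the effect of the intervention on executive functions the primary objective. *Sample size calculation* is for a within-between interaction with two groups and four time points.
- Table 2, under *Executive Functions (EFs)*, lists reaction time, accuracy and a composite score for two tasks. For the Corsi task it lists "Block span, total correct sequences, summary score".

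**The concern.** The Friedman test ranks each participant's repeated values and asks whether the visits differ. It cannot say whether the two groups differ, or whether they change differently. The article gives the test a factor that it does not have. This is an error in a stated rule, not a detail left to a fuller document.

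The rule expressly covers primary outcomes. A significant Friedman result for one of them would show that scores changed over time. In children who are growing, repeating the same tests and recovering from treatment, that can happen with no intervention effect. A non-significant result could hide a real group difference.

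Two further losses follow. Allocation is by centre and not randomized, and the Friedman test cannot adjust for baseline imbalance or use elapsed days, both of which the same section wants. Also, the supplementary correlations of baseline with gain are limited to outcomes with a significant group × time interaction, and a Friedman-analysed outcome can never show one.

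**Working it through.** **1. The plan's own figure.** Inputs from *Sample size calculation*: f = 0.105, retest correlation ρ = 0.8, m = 4 visits, k = 2 groups, α = 0.05, power 80%. For the within-between interaction, with sphericity assumed, λ = f²·N·m/(1 − ρ), df1 = (k − 1)(m − 1) = 3 and df2 = (N − k)(m − 1).

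- N = 52: λ = 0.011025 × 52 × 4 / 0.2 = 11.47, df2 = 150, power 0.811.
- N = 50: power 0.793.
- N = 70: λ = 15.44, df2 = 204, power 0.920.

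The stated N = 52 reproduces. The sample size is not in error, but it is for a test that the Friedman branch does not perform.

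**2. What the Friedman statistic contains.** With R_j the sum over all N participants of their within-person ranks at visit j,

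Q = [12 / (N·m·(m + 1))] · Σ R_j² − 3·N·(m + 1).

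For N = 70 and m = 4 this is (12/1400)·Σ R_j² − 1050. Group membership appears nowhere. As a check, one simulated data set of 70 was reshuffled across group positions. The statistic was 11.40 (p = 0.0097) both before and after.

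**3. What the test would report.** Simulated trials used 35 per group, complete data, unit variance and correlation 0.8 between all visits. The time patterns are assumptions, because the article gives none.

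*No group effect, same trend in both groups.* The reference trend is 0, 0.15, 0.20, 0.30 SD at T0 to T3.

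| Common trend | Pooled Friedman rejects |
|---|---|
| none | 5% |
| one quarter of reference | 10% |
| one half | 28% |
| reference | 83% to 86% over three runs |
| 1.5 times reference | 99% |

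With a trend of 0, 0.2, 0.4, 0.4 SD, Friedman rejected in 99.7%. The group-by-time F test rejected in 4.7%, and a rank test of IG versus CG on T0–T2 change in 5.2%.

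*Real group effect at f = 0.105, groups moving in opposite directions so that the average trend is zero.* Friedman rejected in 3.9%, the interaction F in 91.9% and the rank test of change in 89.4%. At 26 per group the interaction F rejected in 80.5%, which agrees with step 1.

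*Same 0.5 SD group difference, split differently.* Friedman rejected in about 5% for +0.25/−0.25, 26% for +0.4/−0.1 and 67% for +0.5/0. The average changes are 0, 0.15 and 0.25 SD, so the rejection rate follows the average trend.

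These runs used normal data. The Friedman statistic depends only on within-person ranks, so its rates are the same after any increasing transformation of the scores, such as one giving skewed reaction times. Heavy ties, as in block span, are not covered.

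**The case against.** The best defence is that mixed models were meant for everything. After introducing them the section says "For each dependent variable, the optimal model will be determined using likelihood-ratio tests for nested models", without limiting this to normal data. The supplementary analyses offer Spearman correlations for non-normal data among outcomes with a significant interaction, which suggests that interaction tests were expected there too. Convergence need not be an obstacle: in a check with log-normal data, 35 per group and four visits, a random-intercept model with time and group-time converged in 100 of 100 runs.

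This shows that the text is ambiguous, but it does not remove the error. The model-selection sentence sits inside the mixed-model text, and the explicit replacement sentence names only the ANOVAs. The normality condition on the correlations may refer to gain scores. If mixed models were meant for every outcome, the Friedman branch has no purpose and should go.

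Three stronger readings are tempting and are not supported:

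- *That the primary scores will fail the normality check.* Skewed reaction times, bounded accuracy and small-integer spans pooled over ages 6 to 17 make this plausible. However, no distributions are given, the check is graphical as well as Shapiro-Wilk, and composite and summary scores are also listed.
- *That a false-positive or power figure can be attached to the trial.* The rates run from about 5% to 99% with the assumed trend, and the low rate under a real effect needs nearly mirrored changes.
- *That separate Friedman tests per group are planned.* The article does not propose them.

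**Conclusion.** The rule is wrong as written. The article attributes a group factor to a test that has none, and it leaves that test in place for any primary or secondary outcome judged non-normal. Such an outcome would have no test of IG versus CG, contrary to the primary objective and to the interaction for which the trial is sized.

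This conclusion rests on the definition of the Friedman test and on the plain reading that mixed models replace only the ANOVAs. It does not depend on the simulations. How many outcomes would be affected cannot be known from the article: possibly none, plausibly some executive function scores. The sample size figure stands.

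**What to change.** In *Statistical analysis plan*:

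1. Delete the Friedman branch.
2. State that the planned mixed model with the group-time interaction, keeping elapsed days as the time variable, applies to all primary and secondary outcomes.
3. State that distributional checks are made on model residuals.
4. For clearly non-normal outcomes, name in advance a method that keeps a group-by-time term. Options are a transformation (for example log reaction time), a generalized mixed model (for example binomial for accuracy), bootstrap or robust standard errors, or a rank-based factorial longitudinal analysis.

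The cost is a few sentences. Data collection, patient burden and the sample size calculation do not change. The change should be made before outcome data by group are examined, so that the choice of method cannot depend on the results.
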